**3.Methods**

**3.1 Patient Recruitment and Consent**

Patients will be informed about the study during their first visit to the outpatient breast clinic after being informed about their diagnosis and surgical plan. Given the delicate nature of the diagnosis, adequate time will be given to the patients to process the information and when indicated, a second visit will be planned to give them more information about their diagnosis, the proposed treatment plan, and, eventually, their participation in the study. All patients who are interested in the study will be given a patient information form that they can keep and a patient consent form in which they can opt for being sent a copy of the published data of the study. Patients may decide to withdraw from the study at any point before localization is performed.

**3.2 Data collection**

The data collected included baseline patient and tumor characteristics, intraoperative details, and postoperative data including the pathology report, report of complications, and SPIO-induced skin staining.

Preoperative data:

- Age, Sex, BMI
- Radiographic tumour size and BIRADS (both mammogram and Ultrasound)
- Optimal resection volume
- Tumour location (side, quadrant, distance from nipple areola complex)
- Clinical size
- Preoperative core biopsy, needle size
- Histology, grade and receptor status
- Date of SPIO injection, US guided or not and volume
- Date of tumor localization, method employed, radiological guidance, time, and complications of the procedure.

Intraoperative data:

- Date of primary surgery
- Type of procedure
- Sentimag counts in breast and axilla after induction of anaesthesia
- Time from skin incision to specimen excision
- Radiologic margins (min, max)
- Skin excision information
- Sentimag counts on specimen and background
- Specimen weight
- Tracer or tracers that are used
- Successful SPIO SLNB
- Successful SLNB by any method
- Number of SLN
- Axillary procedure

Postoperatice data

- Date of pathology report
- Date answer was delivered to patient
- Specimen dimensions
- Histology and grade
- Size
- Receptor status
- Margin status and closest margin
- SLN number, number of metastases if any in SLN
- Skin staining and size
- Residual magnetic signal
- Planned reoperation
- Breast specific complications within 30 days, CD and CCI grading
- BREAST-Q preoperative, expectations, immediate postoperative, 6 months postoperative, 12 months postoperative

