**List of Abbreviations**

| **ARV** | **Actual resection volume** |
| --- | --- |
| **ARR** | **Actual resection ratio** |
| **DB** | **Blue Dye** |
| **BCS** | **Breast Conserving surgery** |
| **CDCG** | **Clavien Dindo Complication Grade** |
| **CCI** | **Comprehensive Complication Index** |
| **CRF** | **Case Report Form** |
| **DCIS** | **Ductal Cancer In Situ** |
| **FNA** | **Fine Needle Aspiration** |
| **MRI** | **Magnetic Resonance Imaging** |
| **ORV** | **Optimal Resection Volume** |
| **PREMs** | **Patient Reported Experience Measures** |
| **PROs** | **Patient Reported Outcomes** |
| **QoL** | **Quality of Life** |
| **RCT** | **Randomized Controlled Trial** |
| **RFID** | **Radiofrequency identification** |
| **RI** | **Radioisotope** |
| **RSL** | **Radioactive seed localization** |
| **SLN** | **Sentinel Lymph Node** |
| **SLND** | **Sentinel Lymph Node Dissection** |
| **SPIO** | **Superparamagnetic iron oxide nanoparticles** |
| **VAB** | **Vacuum Assisted Biopsy** |

|  |  |
| --- | --- |
| **Summary** |  |
| Title | Magnetic marker or guidewire localization of non-palpable breast cancer in combination with magnetic sentinel lymph node dissection. An open- label, phase 3, pragmati,crandomizedd controlled trial. |
| Clinical Relevance/Background | Preoperative tumour localisation for non- palpable breast cancer lesions has been traditionally performed with a Guidewire. This method is widely available, inexpensive and most of the radiologists and surgeons are familiar with it. However, drawbacks of this technique, including risk of migration, patient discomfort and logistical challenges have led to the development of alternative localisation methods, including magnetic seeds. Previous large cohorts have showed favourable outcomes of magnetic seed localisation, however this has not been investigated in a randomized trial. Furthermore the combination of a totally magnetic technique for lesion localisation and sentinel lymph node detection has not been examined. |

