**2.2 Objectives**

**2.2.1 Primary Objective**

1. The primary objective is a composite of the three components of successful breast conserving surgery for early breast cancer. These components include the re-excision rate, minimal excess tissue removal, and successful SLN detection. The aim of this trial is to compare these three variables between the two arms.

The hypotheses to be tested are:

1. Magnetic marker lesion localization is not equivalent to guidewire localization in terms of re-excision rates due to inadequate surgical margins. Adequate margins are considered “no tumour on ink” for invasive cancer and 2 mm for pure DCIS and will be assessed by specialized breast pathologists.

2. Magnetic marker lesion localization is not equivalent to guidewire localization in terms of excess tissue removal. This will be expressed as the resection ratio and will be assessed by the ratio of the Optimal Resection Ratio (ORV) to the Actual Resection Ratio (ARV).

- ORV will be calculated for each tumour based on the radiological dimensions of the tumor (in cases of discordance between different modalities, the largest dimension will be used) using the volume calculation formula for ellipsoid tumours
[figure not shown]
, where *r*1= x radius +1cm, *r*2=y radius+1cm, *r*3= y radius +1cm. In all dimensions, 1 cm is added as it is the universally accepted macroscopic margin for breast lesions^26^.

ARV will be calculated based on the specimen weight.

Optimally, the ratio $\frac{ARV}{ORV}$ should be as close to 1 as possible to ensure that no unnecessary tissue is removed which may jeopardize the cosmetic and functional outcomes of a breast conserving operation.

3. The combination of magnetic markers and SPIO is not equivalent to the combination of a guidewire and SPIO for SLN detection.

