**2.2.2. Secondary Objectives**

1. Evaluation of the frequency of adverse events, that is, failed localization and postoperative complications, with each method.

2. Time to specimen and total operative time for each technique.

3. The evaluation of healthcare personal experience with each technique via Likert scale items

4. Evaluation of patients’ QoL through PROs and their experience with each technique via PREMs questionnaires.

5. Cost-effectiveness analysis for each technique.

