**6. Safety Reporting**

**6.1 Adverse events**

An adverse event refers to any negative or unintended medical occurrence that is associated with medical intervention, including adverse drug reactions, treatment-related symptoms or diseases, or other adverse experiences that happen during the course of a clinical trial. These events can be mild, serious, or life-threatening, and can range from minor side effects to serious injury or death.

All adverse events will be reported and documented to the principal investigator and appropriate measures will be applied depending on the severity of the adverse effects.

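### The only graded postoperative complication item in section 3.2 is limited to breast-specific events within 30 days, which is narrower than the adverse-event endpoint and the 2-year follow-up it should serve

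*Protocol*

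**What the plan says.** The itemised postoperative data in Protocol section 3.2 contain a single graded complication item: "Breast specific complications within 30 days, CD and CCI grading". The List of Abbreviations expands CCI as "Comprehensive Complication Index". No listed item covers complications of the axilla or arm, or general complications.

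Other parts of the protocol are wider:

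- The lead-in to section 3.2 promises "postoperative data including the pathology report, report of complications, and SPIO-induced skin staining", without restriction to the breast.
- Section 2.2.2 sets the first secondary objective as "Evaluation of the frequency of adverse events, that is, failed localization and postoperative complications, with each method".
- The Summary names adverse events as a secondary endpoint, with no anatomical limit, and follows patients for postoperative complications over 2 years.
- Section 6.1 states that "All adverse events will be reported and documented to the principal investigator", and section 6.2 has them monitored until they resolve or stabilise.

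Section 3.2 also collects some harms separately. Localisation is covered by "Date of tumor localization, method employed, radiological guidance, time, and complications of the procedure", and skin staining has its own item.

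**The concern.** The data item that looks intended to supply the complication comparison is narrower than the endpoint, both in site and in time. This matters more here than in a breast-only operation. All patients are planned for sentinel node dissection, both arms have axillary mapping with SPIO, and sentinel node detection is one of the three primary components. Hypothesis 3 in section 2.2.1 is directed at that site: "The combination of magnetic markers and SPIO is not equivalent to the combination of a guidewire and SPIO for SLN detection". Read literally, the graded complication record leaves out the part of the operation that this hypothesis concerns.

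What is at stake is the completeness of a named secondary endpoint. A later analysis plan can choose a test or a summary measure, but it cannot supply grades for axillary or general events that the case report form never asked for. A score reported under the name CCI but built from one anatomical site would also lead readers to take it for a patient's whole complication burden.

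**Working it through.** The protocol states no complication rate, no CCI value and no sample size for adverse events, so there is no figure to reproduce. The check compares the relevant places with one another.

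**1. Scope and window by location**

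| Place in the protocol | Site | Window | Graded? |
| --- | --- | --- | --- |
| Summary, secondary endpoints | Not limited | Not stated on that line | Not stated |
| Summary, design and methods | Not limited | 2 years | Not stated |
| 2.2.2, objective 1 | Not limited | Not stated | Not stated |
| 3.2, lead-in | Not limited | Not stated | Not stated |
| 3.2, postoperative item | Breast specific | 30 days | CD and CCI |
| 6.1 and 6.2 | All adverse events | Until resolved or stabilised | No CD or CCI grade |

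Only one row carries a grade, and it is also the only row with a site restriction and the one with the short window.

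**2. Time.** Two years is about 2 × 365 = 730 days, and 30/730 = 4.1%. The graded item therefore covers about 4% of the follow-up time that the Summary gives for postoperative complications. This is a share of time, not of events; the protocol does not say how complications are spread over the 2 years.

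**3. Which source feeds the endpoint.** The protocol does not say. There are two possibilities:

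- If the endpoint is drawn from the item in 3.2, axillary and general complications, and anything after 30 days, are outside the comparison.
- If it is drawn from the reports under 6.1, those events are included, but section 6 asks for no CD grade and no site, and does not link the reports to a between-arm analysis.

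Neither source as written gives a graded comparison of all postoperative complications.

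**4. What can be said about size.** Write the number of complications in one arm as N = N(breast) + N(axilla) + N(general). The item captures N(breast), so the count is understated by the fraction [N(axilla) + N(general)] / N. The protocol supplies none of these terms. The understatement of a per-patient rate is a different quantity: it depends on how many patients have non-breast complications only, because a patient with both kinds is still counted. That is not given either.

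The difference between arms splits in the same way: D = D(breast) + D(axilla) + D(general). The item estimates D(breast) alone. The omitted terms can have either sign or be zero, and both arms have the same SPIO mapping, so no direction of bias follows.

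**5. The CCI.** The protocol expands the abbreviation but does not say how the index is built. Assuming only that adding a complication cannot lower a patient's score, a score built from breast events alone is at most equal to the score over all events.

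**The case against.** The strongest reply is that nothing is lost. Section 6.1 has all adverse events documented, the Summary endpoint uses the same term, and the lead-in to 3.2 speaks of complications without limit. This stands as far as it goes. A reader might infer from 3.2 that non-breast complications go unrecorded, or that they necessarily drop out of the adverse-event comparison; the documents support neither. What the reply does not supply is a grade, a site or a stated link from those reports to the comparison.

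A second reply concerns the suspected mechanism. A reader might infer that, if marker and tracer signals interfere, the resulting harm in the axilla would be invisible. That goes too far. Section 3.2 records Sentimag counts in breast and axilla, the tracers used, sentinel node success by SPIO and by any method, the number of nodes and the axillary procedure, and section 2.2.2 compares total operative time. A longer or wider search would leave traces there. Only the resulting axillary morbidity lacks a graded item.

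Third, the phrase breast specific is undefined and could be shorthand for complications of the breast operation as a whole, sentinel node surgery included. This is possible, and it would remove most of the site restriction. It is not what the words say, and centres could read them differently, which is itself a reason to rewrite the line.

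Finally, the primary comparison rests on re-excision, resection ratio and sentinel node detection, so this point does not touch it. That is correct and limits the weight of the finding.

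**Conclusion.** The point holds as an inconsistency that should be corrected on a secondary endpoint. The sole graded postoperative complication item is narrower in site than the adverse-event endpoint, secondary objective 1 and the safety section, and its 30-day window differs from the 2 years in the Summary. Axillary and general complications are to be documented, but they have no item in the data list and no CD or CCI grade.

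If the complication comparison and the CCI are drawn from this item, they rest on a partial list. That conclusion depends on two readings: that breast specific means located in the breast, and that the listed item, not the safety reports, supplies the endpoint. The protocol confirms neither.

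No numerical size can be attached. A percentage understatement of the complication rate would be guesswork without rates in the protocol, and there is no basis for saying which arm would be favoured. The primary endpoints are unaffected.

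**What to change.** In the postoperative data list of section 3.2:

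- Delete the breast-specific restriction and record every postoperative complication with a site code (breast, axilla, general) and its CD grade.
- Compute the CCI over all of a patient's recorded complications, and report the breast subset as a breakdown.
- State that this item is the source of the adverse-event endpoint in the Summary and of objective 1 in section 2.2.2, and how it relates to the reports under section 6.1.
- Reconcile the 30-day window in 3.2 with the 2-year follow-up in the Summary. If both are meant, say which window applies to which analysis.

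The cost is one additional case report form field and slightly more chart extraction. No extra visits or procedures are needed.

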**4. Expected Outcomes and Significance**

The use of a magnetic technique in nonpalpable breast lesions is expected to facilitate operating logistics without compromising oncological and cosmetic outcomes. The use of magnetic seeds and SPIO allows lesion localization and axillary mapping within a much wider timeframe, which may result in reduced theater costs, more efficient planning, and better working conditions for surgeons and radiologists. It is also expected that patient comfort and satisfaction will increase as they will not have to tolerate a wire protruding from their breast and the stress of having everything done on the operation day.

**5. Potential Risks**

Magnetic seeds and SPIO are nonradioactive and nonallergenic substances. No special protocols must be followed for use or disposal.

Concerns have been raised about the risk of skin discoloration which may happen in certain cases after SPIO injection. While this is not harmful, but it is aesthetically displeasing and may persist for months before it fades. The possibility of skin staining should be discussed with each patient before administration and all steps will be taken to avoid it. According to a recent meta-analysis, skin staining may be contained with smaller doses and peritumoural administration, a practice that will be followed in this trial^28^.

Another area of concern is the incompatibility of Magseed© and SPIO to Magnetic Resonance Imaging (MRI). Non-clinical testing has demonstrated that the marker can be scanned safely in an MRI under the following conditions:

• Static magnetic field of 1.5-Tesla (1.5 T) or 3-Tesla (3 T).

• Maximum spatial field gradient of 4,000 G/cm (40 T/m).

• Maximum MR system reported whole body averaged specific absorption rate (SAR) of 4 W/kg (First Level Controlled Operating Mode).

However, it creates artifacts that affect the diagnostic efficacy of MRI, which is why localization must be done after all diagnostic imaging is completed. SPIO also affects MRI diagnostic accuracy, and the traces left behind during the operation affect postoperative imaging as well. Smaller doses and injection dorsally to the tumour with the intent of removing the whole area along with the tumour are measures that will be taken during this trial to reduce this phenomenon.

**6. Safety Reporting**

**6.1 Adverse events**

An adverse event refers to any negative or unintended medical occurrence that is associated with medical intervention, including adverse drug reactions, treatment-related symptoms or diseases, or other adverse experiences that happen during the course of a clinical trial. These events can be mild, serious, or life-threatening, and can range from minor side effects to serious injury or death.

All adverse events will be reported and documented to the principal investigator and appropriate measures will be applied depending on the severity of the adverse effects.

**6.2 Follow-up of adverse events**

All adverse events will be closely monitored until they are resolved or stabilized. Appropriate actions will be taken in case an adverse event requires further medical care or examinations.

**7. Ethical Considerations**

**7.1 Regulation Statement**

Participants information will be protected under the Personal Data Act. The study will be conducted according to the Declaration of Helsinki (64th WMA General Assembly, Fortaleza, Brazil, October 2013) and the Act on Patient Insurance in Sweden. There will be no financial compensation for study participants or study sites.

**8. Amendment**

Date: April 2020

Purpose: To modify the method of localization for breast lesions in response to the COVID-19 pandemic, in order to prevent delays in planned surgery.

Background: In light of the current COVID-19 pandemic, [Investigator/Sponsor name] has determined that it is in the best interest of the trial participants to allow for increased flexibility in the method of preoperative localization for breast lesions.

Amendment: Effective immediately, trial participants and/or personnel, involved in surgery planning will be allowed to choose the method of localization (guidewire or magseed) that is most convenient for their case and ensures that there will be no delays in their planned operation, regardless of the randomization assignment.

Implementation: The change in method of localization will be documented in the case report form and recorded in the trial database. The randomization assignment will still be recorded, but the choice of localization method will take precedence.

Rationale: This amendment is being made to minimize the burden on trial participants during the COVID-19 pandemic and to ensure their comfort and convenience.

Approval: This amendment has been reviewed and approved by the Swedish Ethics Committee

Signed: [name]

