| Objectives | Primary:   - To examine how a magnetic marker compares to the guidewire in successful lesion localisation, minimal excess tissue removal and negative margins in surgery of non-palpable breast lesions. - To evaluate the combination of a ferromagnetic marker for tumour localisation with Superparamagnetic Iron Oxide Nanoparticle (SPIO) for sentinel lymph node detection (SLND) in early breast cancer treatment.   Secondary:   - To evaluate operative times and logistical efficacy of magnetic markers compared to guidewire in the above setting. - To evaluate patient as well as physician satisfaction with the use of this totally magnetic technique. - To evaluate patient quality of life (QoL) |
| Study Design and Methods | Multicentre Pragmatic Randomized Controlled Trial: Patients with confirmed non-palpable ductal cancer in situ (DCIS) or invasive breast cancer, planned for breast conserving surgery (BCS) and SLND will be randomized in two arms.  Arm 1: Lesion localisation with magnetic marker  Arm 2: Lesion localisation with guidewire  Axillary mapping will be done in both arms with the use of SPIO (1-1.5ml Magtrace ©, Endomag, Cambridge,UK) . In the interest of a pragmatic trial, lesion localisation with a magnetic marker as well as SPIO injection will be performed by either a breast surgeron or a radiologist and within a 14 day window before the operation according to local routines or case-per-case convenience. SPIO will be administered peritumoraly. Guidewire localisation will always be performed by a breast radiologist on the day or at most one day before surgery. All cases of localisation will be performed under local anesthetic.  The performing surgeon will document all relevant data in a case reporting form.  All patients will be followed up for postoperative complications, need for re-excision and QoL assessment for 2 years. QoL assessment will be done via PROs questionnaires and the patients experience will be evaluated with PREMs questionnaires.  All involved disciplines (surgeons, radiologists, co-ordinators) will rate their experience with each technique with Likert scale items. |
| Primary Endpoints | To examine the equivalence of magnetic marker and guidewire in successful localisation of non-palpable breast lesions by comparing:   - Re-excision rate - Resection ratio - Sentinel node detection rate |
| Secondary Endpoints | - Adverse events - Operative time - PROs and QoL evaluation - PREMs and cost- effectives analysis |

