**Table:** **PRECIS-2 scores for trial domains**

| **Domain** | **Score** | **Rationale** |
| --- | --- | --- |
| Eligiblity criteria | 5 | Patients with breast tumours that need localisation- Exclusion criteria related to reaction to the material and not the delivery of the technique. |
| Recruitment Path | 5 | Recruitment performed during routine clinic appointment for surgery planning. |
| Setting | 4 | Study conducted in two university and one county hospital, with various case volumes and level of experience. However, all three centres are in the same country. |
| Organisation intervention | 5 | No prior training or additional resources needed for and of the disciplines involved in the trial. |
| Flexibility-delivery | 5 | No monitor or specific advice on co-intervention. |
| Flexibility -adherence | 5 | No special adherence measures. |
| Follow up | 4 | A 2 year follow up which is not routine in usual care and QoL measurements. |
| Outcome | 5 | Primary outcomes are directly relevant to participants |
| Analysis | 5 | All available data used |

PRECIS-2 wheel

Patients with non-palpable DCIS or invasive breast cancer confirmed by fine-needle aspiration (FNA), core biopsy, or vacuum-assisted biopsy (VAB), which are planned for BCS and SLND, will be asked to participate in the trial. Upon their consent, they will be randomized to either arm 1 (lesion localization with magnetic marker) or arm 2 (lesion localization with guidewire).

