**2.6 Sampling and Data Analysis Plan**

The sample size is calculated based on the principle of equivalence, allowing for the detection of a significant difference in resection ratios of 0.3 adjusted for a non-inferiority margin of 4% for re-excision rates and SLN detection. The literature suggests a resection ratio for the guidewire between 2-2.8. To obtain robust results, we lowered that to 1.8 and accepted a 1.5 resection ratio for the totally magnetic technique stemming from our previous pilot study ^25^. Two-sided p-value is set at 0.05 and power to 80%. An additional 10% to sample size calculation will be recruited as inflation to pragmatic settings and tolerance.

The participants will be randomized with an allocation ratio of 1:1 in blocks of 8. The R-Randomizer package will be used for the randomization. The allocated arms will be in dark envelopes, and neither of the involved disciplines will be able to know the arm in which the participants will be randomized beforehand. All participants will receive a code upon randomization consisting of the first three letters of the recruiting center and a number that will be consecutive. The data will be collected by appointed research coordinators.

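### The April 2020 amendment lets the chosen localisation method override the randomised arm, with no closing date and without saying whether the choice also governs the analysis

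*Protocol*

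**What the plan says.** Section 8 of the Protocol, dated April 2020 and effective at once, states that participants and/or the staff planning surgery "will be allowed to choose the method of localization (guidewire or magseed) that is most convenient for their case", provided that the planned operation is not delayed, and that they may do so "regardless of the randomization assignment". Its rationale is "to minimize the burden on trial participants during the COVID-19 pandemic and to ensure their comfort and convenience". On implementation, the change of method is documented in the case report form and the trial database. Then: "The randomization assignment will still be recorded, but the choice of localization method will take precedence". The section gives no closing date, no cap and no case-level criterion beyond convenience and avoiding delay.

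Elsewhere, the Summary gives the primary aim as "To examine the equivalence of magnetic marker and guidewire in successful localisation of non-palpable breast lesions by comparing" re-excision rate, resection ratio and sentinel node detection rate. Section 2.6 sizes the trial on a resection-ratio difference of 0.3 (1.8 against 1.5) and a 4% non-inferiority margin for re-excision and sentinel node detection, with two-sided 0.05, 80% power and concealed 1:1 allocation. It adds: "An additional 10% to sample size calculation will be recruited as inflation to pragmatic settings and tolerance". Switching of method is not mentioned there.

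On how patients are grouped, the PRECIS-2 table in Section 2.4 says only "All available data used", and Section 2.7 names tests between groups without defining the groups.

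**The concern.** Every primary comparison depends on what the two groups are. Section 8 breaks the link between assignment and method received, and the rest of the Protocol does not say which of the two defines the groups.

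- **Precedence governs the analysis.** Patients are then grouped by a method that they or the staff chose. Randomisation no longer protects the comparison, and the document offers no way to bound the selection bias.
- **Precedence governs delivery only, and arms are compared as randomised.** Randomisation is kept, but each arm now contains patients localised by the other method, so the observed difference shrinks. In a superiority question that is conservative. Here the aim is equivalence, with a non-inferiority margin on two endpoints, so shrinkage makes the favourable conclusion easier to reach when it is false. It also removes power from the 0.3 resection-ratio difference.

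**Working it through.** **No figure to reproduce.** The Protocol gives no sample size, standard deviation, control re-excision rate, sentinel node detection rate or switching rate. The stated design point (0.3, two-sided 0.05, 80% power, 4% margin) is taken as given. The switching and event rates below are assumptions.

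**Dilution.** Let c be the switching proportion in one arm plus that in the other. If switching is unrelated to prognosis, the as-randomised difference is the true difference × (1 − c). Switching of 20% in one arm only and 10% in each arm both give c = 0.20.

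**Resection ratio.** For a comparison designed at 80% power, power = Φ((1 − c)(1.960 + 0.842) − 1.960). This needs neither the standard deviation nor the sample size. The last column multiplies the first term by √1.1 to credit the planned 10% inflation in full.

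| c | Difference | Power | Power with 10% inflation |
|---|---|---|---|
| 0 | 0.30 | 80% | 84% |
| 0.10 | 0.27 | Φ(2.521 − 1.960) = 71% | 75% |
| 0.20 | 0.24 | Φ(2.241 − 1.960) = 61% | 65% |
| 0.40 | 0.18 | Φ(1.681 − 1.960) = 39% | 42% |

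To hold 80%, the sample size must be multiplied by 1/(1 − c)²: 1.23, 1.56 and 2.78. The 10% inflation offsets only 1 − 1/√1.1 = 4.7% total switching, about 2.3% in each arm, and only if none of it is used up by other losses.

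**Re-excision against the 4% margin.** Assume control rates of 5%, 10% and 15%. The size per arm that the margin needs at one-sided 0.025 and 80% power is (2.802)² × 2p(1 − p)/0.04², or 467, 883 and 1,251. Set the true excess with the marker at exactly 4 points, so that any non-inferiority claim is false, and split switching equally between arms. The false-claim rate is Φ((0.04 − d)/SE − 1.960), where d is the diluted excess and SE uses the unpooled variance of the two diluted rates.

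| c | Diluted excess | 5% control | 10% control | 15% control |
|---|---|---|---|---|
| 0 | 4.0 points | 2.5% | 2.5% | 2.5% |
| 0.10 | 3.6 points | 4.3% | 4.5% | 4.5% |
| 0.20 | 3.2 points | 6.9% | 7.5% | 7.7% |
| 0.40 | 2.4 points | 15.9% | 17.8% | 18.6% |

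Example for 10% control and c = 0.20: the diluted rates are 10.4% and 13.6%, SE = 0.01545, and Φ(0.008/0.01545 − 1.960) = 7.5%.

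**Grouping by method received.** No arithmetic applies. Dilution disappears, but it is replaced by a selection bias that the document gives no means to size.

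**The case against.** A reader might infer that the Protocol prescribes analysis by method received. The text does not support that. The precedence sentence stands under implementation, next to how the change is documented, and the amendment's purpose is to prevent surgical delay, so delivery of care is a natural reading. The assignment is still recorded, which leaves an as-randomised analysis open. The PRECIS-2 entry concerns which data are used, not how patients are grouped. What stands is the ambiguity.

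A reader might also say that convenience alone overrides randomisation, indefinitely. Section 8 joins convenience with avoiding delay and ties both to the pandemic. It is still true that no closing date is stated.

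It is tempting to name the confounders, such as lesion type or radiologist availability, and to say that they drive re-excision or specimen size. The document does not show this. Only the general concern about chosen groups is supported.

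The size may be smaller than the worst rows above. Switching could be one-sided, since Sections 1.2.1 and 4 describe the wire as the harder method to schedule; 20% in one arm only is the c = 0.20 row, not the 0.40 row. Patients localised before April 2020 are unaffected.

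Finally, analysis sets are commonly left to a statistical analysis plan, and one not shown may define them. Their absence alone is therefore no finding. But such a plan cannot restore adherence to the assigned arm, and an as-randomised analysis there would sit beside a Protocol saying that the choice prevails.

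**Conclusion.** The concern holds as a defect in operative Protocol text: an override of allocation with no closing date, and a precedence clause that does not say whether it reaches the analysis. On one reading the comparison is not randomised. On the other it is diluted in the direction that favours equivalence and non-inferiority.

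The size is illustrative. Total switching of 10 to 40% takes resection-ratio power from 80% to between 71% and 39% before inflation, and false non-inferiority on re-excision from 2.5% to between about 4% and 19%. These figures rest on assumed switching rates, an assumed control re-excision rate of 5 to 15%, a sample of the size the margin would need, switching not strongly related to prognosis, and switching across the whole sample. Patients enrolled before the amendment reduce the effect. Because all three primary endpoints depend on how groups are formed, this should be settled before analysis.

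**What to change.** In Section 8:
- limit the precedence wording to delivery of care;
- state the dates during which the override applied.

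In Section 2.7, state that:
- the primary analysis compares arms as randomised;
- for the two endpoints with the 4% margin, the conclusion must also hold in a per-protocol set, meaning patients who received the assigned method;
- switching is reported by arm and by period;
- a sensitivity analysis excludes patients randomised in the amendment window.

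**Cost.** No new data are needed, because both the assignment and the change of method are already recorded. The per-protocol set is smaller and is itself open to selection, since patients leave it by the same choice that causes the problem; agreement between the two analyses is the safeguard, not either one alone. Requiring agreement costs power: losing 20% of patients takes 80% to Φ(2.802 × √0.8 − 1.960) = 71%, or about 75% if the 10% inflation is fully available (√0.88 in place of √0.8). As-randomised estimates may also look smaller. No change to the clinical choice of localisation method is proposed.
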